### Randomization and Group Allocation

Randomization takes place in the form of assigning the participants according to a set of randomized numbers generated by a computer software (Excel 2020, Microsoft Cooperation). The randomization ratio is 1:1. Once randomization is executed, sealed envelopes are used for each participant and group allocation is performed accordingly.

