## Abstract

**Background:** Burn patients experience major physiological and psychological stressors during treatment and rehabilitation, including elevated levels of pain, anxiety, stress, or depression. Music interventions inclusive of music therapy (MT) have been shown to improve such symptoms, but rigorous clinical trials investigating specific music therapy methods in adult burn patients are scarce.

**Methods:** This is a single center Randomized Controlled Trial (RCT) protocol with two parallel arms. Participants are 81 adult burn patients admitted to the Intensive Care Unit (ICU) of the University Hospital Fundación Santa Fe de Bogotá in Colombia. The intervention consists of a Music Assisted Relaxation (MAR) protocol, a music therapy technique composed of entrained live music combined with a guided relaxation and/or the use of imagery. The effects of the MAR will be compared to a control group (treatment as usual) over a period of maximum 2 weeks or six interventions. The primary outcome measure is perceived background pain, as measured with a Visual Analog Scale (VAS) before and after each intervention. Secondary outcomes are anxiety and depression levels; vital signs; and the use of pain medication. Additionally, some patients in the intervention group will be invited to participate in electroencephalography, electromyography, and electrocardiography recordings during the MAR.

**Discussion:** This study protocol follows the SPIRIT guidelines for defining items of clinical trials and is the first study in Colombia to evaluate the effects of music therapy for adult burn patients. With this RCT it is hoped to gather new knowledge about the potential of music therapy to help critical care patients cope and recover from their injuries during the hospitalization in the ICU.

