### Participants and Sample Size Calculation

The sample size was calculated according to the Asymptotic normal method (40). Obtaining a power of 80% and taking a *p*-value of 5%, the number of participants expected to have in the study is *n* = 81, which is similar to other studies in the field (30, 31). The formula used for calculating the sample size (40, 41) is:

$$\begin{array}{l} n=\frac{{\left[Z\left(\alpha /2\right)\sqrt{\left(2P\left(1-P\right)\right)}+Z\left(\beta \right)\sqrt{\left(P1\left(1-P1\right)+P2\left(1-P2\right)\right)}\right]}^{2}}{{\left(P1-P2\right)}^{2}} \end{array}$$

Where *P* = 0.5^*^(P1 + P2), Power = 1-β and Z(α/2) and Z(β) are taken from the z table. For this particular case, P1 corresponds to the expected outcome in the control group and P2 the expected outcome in the intervention group. The primary outcome measure is the Visual Analog Scale (VAS) that consists of 10 points (100%) and when considering a clinically significant decrease and difference of 2 points (20%), these values would correspond to 80 and 60%, respectively (P1: 80 and P2: 60). Replacing these values in the above equation, the sample size is:

$$\begin{array}{l} n=\frac{{\left[1.96\sqrt{\left((2.07)*(1.07)\right)}+0.842\sqrt{\left(0.8*(1-0.8)+0.6*(1-0.6)\right)}\right]}^{2}}{{\left(0.2\right)}^{2}}\\ \;=81.25\;\approx \;81 \end{array}$$

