### Data Collection and Outcome Measures

Basic socio-demographic and medical data will be collected from all participants, including age; gender; educational level; marital status; level of support by the patient's social system; medical diagnosis; type and location of the burns; and depth and surface % of the burns.

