## Potential Limitations

We have also identified several potential limitations of this study protocol. First, background pain is influenced by many different factors, such as the medical condition of the patient, the number of procedures, mental health, and social support, among others. This means that a diversity of factors can potentially affect the pain perception of patients. This might be different during procedural pain, in which a more direct relationship between the procedure and the pain experience exists and thus immediate effects of music interventions might be observed more consistently. However, as mentioned at the end of the previous section, background pain in burn patients is an under-investigated topic and may be highly relevant for long-term well-being and health. While an accumulative effect of the MAR intervention over time may lead to an improved relaxation response and coping mechanisms and thus to reduced pain levels and improved mental health, little is known about the ideal dosage or frequency of music interventions. Formal moderator/mediator analyses in the fields of music therapy and music medicine may help in addressing such issues and are clearly needed (71–73).

Another limitation might be the broad inclusion criteria, which could affect the statistical power of the study. This was chosen since recruitment during COVID pandemic might be slower than expected, as ICU beds usually are prioritized for COVID patients during each infection peak. Thus, to keep recruitment within a feasible time frame, this study does not focus on a specific patient group within the burn population.

And third, other outcome measures including EEG, EMG, and ECG measurements are an exploratory feature of this study and due to the small sample size, the results can thus not be generalized. However, we consider them as important first steps in materializing the need for describing potential neurophysiological pathways and mechanisms of live MAR interventions based on the principles of entrainment.

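### The article names no blocking, stratification or adjustment for burn severity, although burn surface is known before allocation; using it would give a modest gain in precision and credibility

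*Protocol article*

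**What the plan says.** All references are to the protocol article.

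- **Randomization and Group Allocation.** The method is "assigning the participants according to a set of randomized numbers generated by a computer software" (Excel). "The randomization ratio is 1:1", and "sealed envelopes are used for each participant and group allocation is performed accordingly". No block, stratum, minimisation or fixed arm total is named; none is ruled out either.
- **Abstract.** "Participants are 81 adult burn patients admitted to the Intensive Care Unit (ICU"). Other Outcome Measures equates 20% of the intervention group with about eight patients, so about 40 per arm are planned.
- **Data Collection and Outcome Measures; Table 1.** The baseline medical data include "depth and surface % of the burns". Table 1 marks these data in the enrolment column, ahead of the allocation column.
- **Potential Limitations.** Background pain is said to depend on many factors, the patient's medical condition among them. Inclusion is broad by choice: "this study does not focus on a specific patient group within the burn population". The article concedes that this may affect power.
- **Data Management and Statistical Analysis.** For pain and the secondary outcomes the article lists ANOVA, Student's t-test and the Mann-Whitney test. No covariate is named for these comparisons. It also plans a baseline comparison of the groups and a closing logistic regression described in general terms.

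**The concern.** The article recognises that its patients are mixed and that their condition affects the primary outcome. It also measures burn severity in time to use it. But it describes no step, in allocation or in the comparison of VAS between arms, that does use it. With about 40 patients per arm, a chance difference in burn severity can be large enough to move the VAS estimate visibly and to make a reader doubt the result, whichever way it falls. What is at stake is precision and credibility, not bias.

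**Working it through.** **Inputs from the article.** N = 81 in total, ratio 1:1, so 40.5 per arm on average; target difference 2 VAS points; two-sided alpha 5%.

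**Assumed, because the article gives no figure.** VAS SD 2.5 (SD 3.2 for the power check in step 4); correlation r of burn surface with the analysed VAS 0.30 to 0.45; stratification at the median of burn surface.

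**1. The article's own figure.** With P = 0.7:

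[1.96·√(2·0.7·0.3) + 0.842·√(0.8·0.2 + 0.6·0.4)]² / 0.2² = [1.270 + 0.533]² / 0.04 = 81.25.

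The 81 reproduces. This formula gives a number per group, while the article uses it as the total. That is a separate matter; 81 in total is used here because that is what the article plans.

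**2. Arm sizes if every patient is an independent draw.** Binomial(81, 0.5):

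| Split | Difference | Probability |
|---|---|---|
| 46:35 or worse | ≥ 11 | 0.266 |
| 50:31 or worse | ≥ 19 | 0.045 |

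**3. Chance imbalance in burn surface, in SD units.**

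- Unrestricted: SD = √(2/40.5) = 0.222. The two-sided 5% point is 1.96 × 0.222 = 0.44.
- Permuted blocks of 4 and 6 within two burn-surface strata (simulation of 20,000 trials): SD 0.138. An imbalance above 0.44 occurs in about 0.1–0.2% of trials, against about 5% unrestricted. The 95th percentile of the arm-size difference is 3, against 17.

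**4. Which part of the remedy does the work.** Uneven arms alone matter little. At an assumed SD of 3.2, power for 2 points is 80.3% at 40:41, 78.5% at 32:49 and 79.8% averaged over all unrestricted splits. Fixing the totals at 40:41 without strata does nothing for severity. The chance of a gap of 15 percentage points or more in a binary severity factor (assumed prevalence 20%, 30%, 50%) is 0.10, 0.15 and 0.18 unrestricted, and 0.10, 0.15 and 0.19 with fixed totals. Of the allocation changes, only stratification (or minimisation) reduces it.

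**5. What this means for the VAS difference.**

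- Shift at the 5% extreme = r × 0.436 × 2.5: 0.33 points (r = 0.30) to 0.49 points (r = 0.45), or 16–25% of the 2-point target. With stratified blocks the corresponding figure is r × 1.96 × 0.138 × 2.5: 0.20 to 0.30 points. About 62% (0.138/0.222) remains.
- Unrestricted standard error = 2.5 × √(2/40.5) = 0.556.
- Share of the variance removed by stratified blocks = r² × [1 − (0.138/0.222)²] = 0.614·r²: 5.5% to 12.4%.
- Standard error then = 0.556 × √(1 − 0.055) = 0.540, to 0.556 × √(1 − 0.124) = 0.520. The gain is 2.8% to 6.4%.
- Linear adjustment for burn surface itself multiplies the standard error by about √(1 − r²), that is 0.954 to 0.893, before the small cost of one extra parameter. Adjustment is therefore at least as useful as the stratified list.

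**The case against.** The case on the other side is strong on several points.

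- **Silence is not a statement.** A reader might infer that the trial has no blocks or strata. The article does not say so. It condenses a fuller protocol that is not shown, and a list permuted in advance to 40 and 41 fits its wording equally well. The 27% and 4.5% apply only if the list is unrestricted. This stands.
- **Simple randomisation is valid.** A reader might infer bias or an inflated error rate. Neither follows: chance imbalance is already part of the standard error and of the 5% alpha. The 0.33–0.49 point shift is a 5% extreme, not a typical result or an extra error. This stands.
- **The later analyses.** A reader might infer that nothing later deals with imbalance. That goes too far. The article plans a baseline comparison and a multivariable regression, and makes medical factors associated with the effect a secondary objective. None of these is stated to be a severity-adjusted comparison of VAS between arms, so the gap narrows but does not close. VAS is also measured before and after each session; if change is analysed, stable severity differences partly cancel, r falls and the gain shrinks.
- **COVID waves.** A reader might infer drift in ICU care over the pandemic. The article says only that "ICU beds usually are prioritized for COVID patients during each infection peak", as a reason for slow recruitment. It reports no effect on care or pain, so this gives no ground for the point.
- **Burn surface is one choice among several.** The article lists procedures, mental health and social support as well. Burn surface is proposed because it is measured before allocation, not because the article shows it to be the strongest predictor.

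**Conclusion.** The point holds as a modest design improvement. The article describes an allocation method without restriction or strata, and VAS comparisons without a severity covariate, in a population that it calls broad and with burn surface on record before allocation. Stratified blocks would lower the SD of the burn-surface imbalance from about 0.22 to 0.14 and the standard error by roughly 3–6%. The first figure assumes an unrestricted list of 81 and a median split. The second also needs a correlation of 0.30–0.45, which the article does not supply; with a weaker correlation the gain is smaller. Uneven arms by themselves cost about 2 power points or less even at 32:49. The trial's validity is not in question.

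**What to change.** In Randomization and Group Allocation, state the method. Use randomly permuted blocks of mixed size (for example 4 and 6, not disclosed to recruiting staff), stratified by burn surface in two classes at a cut that the investigators set in advance, with a stored list and one envelope series per stratum. In Data Management and Statistical Analysis, include burn surface or the stratum in the comparison of VAS between arms. Otherwise the reported standard error does not reflect the gain from stratifying.

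If recruitment has already started, keep the existing list and prespecify the adjustment for burn surface before the analysts see results by arm. On the figures above, that alone secures the gain in precision.

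The cost is a regenerated list, two envelope series with slightly more handling, and a little added predictability in an open single-centre trial, which undisclosed mixed block sizes limit. Adjustment costs one model term and no new data.

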### Blinding

Due to the nature of the intervention, blinding participants to the result of the randomization is not feasible. However, data collection takes place by blinded research assistants and data analysis will also take place by researchers blinded to the outcomes of the randomization.

### Intervention

Participants in the intervention group will take part in a Music Assisted Relaxation (MAR) protocol. MAR is a music therapy technique that includes listening to live music based on the principles of entrainment (42, 43), combined with deep diaphragmatic breathing and guided relaxation and imagery. In the first step, the procedure of the intervention is explained to the patient, and he/she is asked to close the eyes or focus on a fixed point on the ceiling or wall. This is followed by a verbal introduction focusing on body and respiratory awareness. A mental image is then introduced, for example: sitting on a beach watching the waves of the sea; being on top of a mountain contemplating the horizon; imagining a personalized safe and comfortable place; among others. The patient is asked to breathe with the music while concentrating on the imagery and sounds. While the improvised music can change according to each patient and situation, it usually consists of a slow tempo, simple harmonic structures, free-flowing melodies, avoiding large intervals or abrupt changes in tonalities. The musical instruments used are a classical guitar with nylon strings (Yamaha C-40), an ocean drum (a drum with a double skin over which small metal pallets role imitating the sound of waves) and a Samafon (an instrument consisting of aluminum/copper tubes of different sizes that are stuck with a soft mallet producing long-lasting single or combined tones). Once the music stops, the patient is asked to become aware and the experience during the session is verbally elaborated. Each intervention will last between 30 and 40 min and will be delivered three times per week from the day of study entry up to a maximum of 2 weeks or six interventions in total. The time frame and frequency of the interventions has been chosen to stay close to daily clinical practice, in which the music therapy team of the FSFB usually sees patients 2-3 times per week. This has been a therapy frequency working well in terms of being able to offer a process-oriented approach, but not to overstrain patients due to their numerous commitments with other therapies and medical procedures. With respect to the time frame, burn patients stay in the ICU of the FSFB an average of 13,9 days, with 42% staying up to 1 week, 19% up to 2 weeks, and 38% more than 2 weeks. However, depending on the medical condition, it might take a couple of days or more from admission onwards until the patient is medically stable enough to start therapy. Thus, an intervention period of 2 weeks was chosen to capture most of the population. The musical instruments are disinfected and cleaned according to a protocol that has been published elsewhere (44).

Participants in the control group receive treatment as usual (TAU) according to the attending physician. An environmental control will be imposed for the control group to equalize basic conditions during data collection including promoting a resting posture, interrupting care procedures unless absolutely necessary, and keeping the room doors closed.

### Data Collection and Outcome Measures

Basic socio-demographic and medical data will be collected from all participants, including age; gender; educational level; marital status; level of support by the patient's social system; medical diagnosis; type and location of the burns; and depth and surface % of the burns.

### Primary Outcome Measure

Primary outcome measure is a Visual Analog Scale (VAS) of 0-10. 0 indicates a state without any pain and 10 indicates the most severe pain possible. Each number from 0 to 10 is distributed in a line 1 cm apart and the patient can mark the intensity of pain felt at the time of filling out the VAS. The VAS will be applied at baseline, and every time before, after, and at 3 h post-each intervention. Period of data collection: maximum 2 weeks from the point of study entry.

### Secondary Outcome Measures

The Colombian version of the Hospital Anxiety and Depression Scale (HADS) (45) will be applied to measure anxiety and depression levels of the participants. The HADS consists of a 7-item anxiety subscale and a 7-item depression subscale rated on a four-point Likert scale. The higher the total points on each scale, the greater the risk of a depressive or anxiety disorder, with a maximum score of 21 for each subscale. The HADS scale will be applied at baseline, after the third, and after the last intervention. Period of data collection: maximum 2 weeks from the point of study entry.Vital signs (heart rate, respiratory rate, oxygen saturation, blood pressure) will be measured via hospital monitors before the intervention, after the intervention, and at 3 h post-intervention. Period of data collection: maximum 2 weeks from the point of study entry.The use of pain medication refers to the frequency and dose of additional analgesic medications requested by the patient during the study period (complementary or rescue doses). The total amount of dosage and frequency will be calculated by summing up individual records. Period of data collection: maximum 2 weeks from the point of study entry.

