**Interventions**							
Intervention group			**x**	**x**	**x**	**x**	
Control group			**x**	**x**	**x**	**x**	
Assessments							
Baseline measures:	**x**						
Socio-demographic/Medical data	**x**						
VAS	**x**						
HADS							

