**Outcome measures**							
VAS			**x**	**x**	**x**	**x**	**x**
HADS					**x**		**x**
Vital signs			**x**	**x**	**x**	**x**	**x**
Medication usage			**x**	**x**	**x**	**x**	**x**

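### Vital signs and pain-medication use, two of the three secondary outcomes, have no measurement scheduled before allocation; adding one would be a cheap gain in precision

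*Protocol article*

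**What the plan says.** The measurement times of the three secondary outcomes and the primary outcome are set out in the protocol article's outcome sections and in Table 1 (Participant Timeline).

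- **Pain VAS** (Primary Outcome Measure): "The VAS will be applied at baseline, and every time before, after, and at 3 h post-each intervention".
- **HADS** (Secondary Outcome Measures): "The HADS scale will be applied at baseline, after the third, and after the last intervention".
- **Vital signs** (Secondary Outcome Measures): they "will be measured via hospital monitors before the intervention, after the intervention, and at 3 h post-intervention". No separate baseline is named.
- **Pain medication** (Secondary Outcome Measures): the outcome covers "additional analgesic medications requested by the patient during the study period (complementary or rescue doses", and it is summarised as a sum: "The total amount of dosage and frequency will be calculated by summing up individual records".

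In Table 1 the block headed "Baseline measures" lists socio-demographic and medical data, VAS and HADS. The vital-signs row and the row "Medication usage" carry crosses only from t1 to closeout; allocation is at t0. The crosses in the baseline block appear one row out of place in the text at hand. This is taken as a fault of extraction, since the prose confirms the HADS baseline.

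The Blinding section says that participants cannot be blinded. The control arm has matching data-collection occasions: "An environmental control will be imposed for the control group to equalize basic conditions during data collection".

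**The concern.** VAS and HADS each have a value that allocation cannot have influenced. Vital signs and medication use do not.

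For medication, nothing at all is recorded before the study period. Demand for extra analgesia can be expected to differ widely between burn patients, and a patient's recent demand is a natural predictor of later demand. Without it, the arms cannot be compared on prior use, and the analysis cannot remove that part of the between-patient variation. The outcome matters to the authors: the Discussion notes that earlier trials in adult burn patients did not replicate a reduction in opioid intake, and says that this trial will look at the question through rescue doses.

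For vital signs, the first reading comes just before the first session. By then patients in the intervention arm know that a relaxation session is about to start, and controls know that it is not. Heart rate, respiratory rate and blood pressure could respond to that knowledge. A reference value that allocation may have touched is a weaker covariate or anchor for change than one taken before the envelope is opened.

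**Working it through.** **1. Schedule, side by side**

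| Outcome | Named baseline in text | In the pre-allocation block of Table 1 | First scheduled value |
|---|---|---|---|
| VAS | yes | yes | before allocation |
| HADS | yes | yes | before allocation |
| Vital signs | no | no | before session 1, after allocation |
| Pain medication | no | no | on-study doses only |

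The VAS sentence lists the baseline and the pre-session reading as two separate items, so the protocol itself distinguishes them. The medical data listed under Data Collection and Outcome Measures (diagnosis; type, location, depth and surface of the burns) include neither vital signs nor analgesic use.

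**2. Numbers per arm**

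The only computed figure in the protocol is the sample size. With P1 = 0.8, P2 = 0.6 and P = 0.7:

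[1.96 × √(2 × 0.7 × 0.3) + 0.842 × √(0.16 + 0.24)]² / 0.2² = (1.270 + 0.533)² / 0.04 = 81.25.

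This reproduces the stated value. The present point does not depend on it, except that 81 participants at 1:1 give about 40 and 41 per arm. The Other Outcome Measures section agrees: about eight participants as 20% of the intervention group implies 8 / 0.2 = 40.

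**3. Chance imbalance in an unrecorded baseline**

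SD of the standardised difference = √(1/40 + 1/41) = 0.222. The 95% range is ±1.96 × 0.222 = ±0.44 SD. This holds for any covariate in any trial of this size, and shows only how large an unseen imbalance could be.

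**4. Precision forgone**

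Let r be the correlation of the baseline with the on-study outcome. The documents give no value, so r = 0.3 to 0.7 is an assumption. In a linear model the residual variance is multiplied by 1 − r², and the equivalent sample-size factor is 1/(1 − r²). The detectable difference at 80% power and two-sided 5%, taking 40 per arm, is (1.96 + 0.842) × √(2/40) × √(1 − r²).

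| r | Variance left, 1 − r² | Equivalent patients, 1/(1 − r²) | Detectable difference (SD) |
|---|---|---|---|
| 0 (no covariate) | 1.00 | 1.00 | 0.63 |
| 0.3 | 0.91 | 1.10 | 0.60 |
| 0.5 | 0.75 | 1.33 | 0.54 |
| 0.7 | 0.51 | 1.96 | 0.45 |

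These gains are measured against no covariate. For vital signs the pre-session-1 reading could already supply much of the gain. For medication, burn depth, burn surface and baseline VAS could supply part of it.

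**The case against.** The case on the other side is substantial, and most of it stands.

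- **Vital signs are not without a pre-treatment value.** The reading before session 1 precedes any exposure to the intervention, and the control arm has matching occasions. HADS needs a named baseline because it has no pre-session reading; vital signs do have one. This stands. What remains is that the reading follows open allocation, and the anticipation effect is conjecture, with neither size nor direction known.
- **Medication is a cumulative total.** Compared between randomised arms, it needs no baseline to be unbiased, and the statistical section states no change-from-baseline analysis that would fail. A chance imbalance is part of the ordinary type I error that the 5% test already covers. This stands. The loss is one of precision and of the ability to check balance.
- **Partial adjustment is already possible** through burn depth, burn surface and baseline VAS. This stands too, but these are proxies for prior demand and do not measure it.
- **The linear-model formula may flatter the gain.** Summed extra doses may be skewed or contain many zeros, and the plan allows for a Mann-Whitney test. This is a fair caution on the size.
- **The chart could be searched later, and covariates can be left to the SAP.** This is partly right. The choice of model can wait for the SAP. But Table 1 is an explicit schedule, and data taken prospectively to one definition are more dependable than later retrieval.

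A reader might infer that these endpoints have no usable baseline, cannot be analysed, or give a biased comparison. The documents do not support that, for the reasons in the first two items. Nor are these two of three secondary objectives: the Objectives section lists five, and three is the number of secondary outcomes in the Abstract.

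**Conclusion.** The point holds as a limited one. The protocol schedules no measurement of vital signs or pain-medication use before allocation, in contrast to VAS and HADS. The medication half is the stronger, because no pre-study value of any kind is planned. The vital-signs half is smaller, because a pre-treatment reading exists in both arms and its only weakness is that it comes after open allocation.

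The cost is precision for two secondary outcomes: a factor of about 1.1 to 2 in equivalent patients for r between 0.3 and 0.7, against an analysis with no covariate, and less where existing covariates or pre-session readings are used. This rests on the assumed correlations, on about 40 patients per arm, and on a linear model. That prior rescue use strongly predicts later use is plausible, but the documents do not show it. Nothing is miscalculated, and neither endpoint is invalidated.

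**What to change.** Add both items to the t-1 (enrolment) column of Table 1, for both arms:

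- from the medication chart, the number and dose of requested or rescue analgesics in the 24 h before allocation, expressed per hour where the look-back is shorter;
- from the monitor, one resting set of vital signs, taken with the baseline VAS before the envelope is opened.

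Use each as a covariate when the arms are compared on that outcome. A plain Mann-Whitney test takes no covariate, so a regression or analysis of covariance is needed for this; its form can be left to the SAP. Keep the pre-session readings as repeated measures. The 24 h window is a proposal and has no source in the protocol.

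The cost is one extra line on the baseline form, filled from sources the hospital already keeps, with no added procedure and no change to care. The downside is a shorter look-back for patients enrolled soon after admission. The Intervention section says that patients may need a couple of days or more from admission before they can start therapy, so a full 24 h should often be available. Because sedated and ventilated patients are excluded, some may have come off sedation shortly before enrolment and could not have requested doses for part of the window; the form should record this.
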